### Biomarkers analysis

The Andromeda study includes molecular analyses to evaluate circulating miRNAs and SNPs that will be performed blindly on an appropriate case-control sample extracted from the cohort of enrolled women, as soon as a minimum number of BC cases will be reached. Blinding allows avoiding that knowledge of subject’s outcome status affect the interpretation of an assay result or the care with which the specimen is handled. The prospective specimen collection plus retrospective blinded-evaluation (PRoBE) design assumed here has been proposed by Pepe et al. [29] as a good practice to follow for the pivotal evaluation of biomarker accuracy.

The selected miRNAs come from two consolidated studies [20, 21], and are suited to the screening nature of the Andromeda study.

In more detail the biomarkers to be analyzed are the following:Circulating total RNA extraction from plasma samples will be carried out with miRNeasy serum/plasma minikit (Qiagen) with minor modifications of the Exiqon protocol, implying use of a RNA carrier (batteriofage MS2 RNA, Roche Diagnostics®) to promote RNA precipitation. Cel-miR-139 will be used as spike-in control to check extraction yield and to normalize data. RNA samples will be purified on membranes and eluted with nuclease free water and stored at −80 °C. We will carefully evaluate the presence of haemolysis in our analysis and exploit our huge sample cohort to validate previous results on an independent dataset.RT-qPCR analysis of selected markers (genes, microRNAs, lncRNAs)Total RNA samples will be reverse-transcribed and amplified with specific assays for cel-miR-39, hsa-miR-1228, hsa-miR-145, hsa-miR-451, hsa-miR-222, hsa-miR-18a, hsa-miR-181a and analyzed on a qPCR apparatus with specific dedicated software. Every RNA samples will be analyzed in triplicate. Normalization of expression data will be carried out using hsa-miR-1228 [30] and cel-miR-39 as normalizers. As for SNPs also for miRNAs research findings are continuously updated, so they will be selected considering the most recent findings at the time of their extraction [31].SNP genotypingGenomic DNA will be extracted from buffy coat with High Pure PCR Template preparation kit (Roche Diagnostics®). 77 SNPs described in Mavaddat et al. [18] will be evaluated using the Personal Genome Machine (Ion Torrent) NGS apparatus.

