### Statistical power and analysis

All the data collected through the SRQ will be used to obtain the risk estimates based on a risk prediction model that has been developed for the Italian population and validated on an independent cohort of Italian women (Petracci score) [32].

This information, along with the information on breast density, lifestyle related risk, polygenic risk score from miRNAs and SNPs will be modeled in respect of BC risk factors onset.

As they are determined on the same subjects, among women with abnormal mammography, the most efficient estimate of the ratio between relative (positive vs negative) positive predictive values (PPV) ratios, for any couple of the above factors is given by:$$ PPV\; ratios=\frac{cancers\;\left(\kern0em positive to factor1\; but\; not to factor2\right)\kern0.5em \times \kern0.5em non cancers\;\left(\kern0em positive to factor2\; but\; not to factor1\right)}{cancers\;\left(\kern0em positive to factor2\; but\; not to factor1\right)\kern0.5em \times \kern0.5em non cancers\;\left(\kern0em positive to factor1\; but\; not to factor2\right)} $$

Assuming that 40% of 21,000 enrolled women have a dense breast, 20% a certain Petracci score, 50% a lifestyle risk and 20% a given miRNA, that 11‰ of study women carry BC and that the overall PPV of mammography is 20%, some 100–120 discordant cancers and 640–740 discordant women with abnormal mammography but no cancer are expected for the considered couples of factors. Under these assumptions, the study has about 80% power to reject (alpha = 0.05) the null hypothesis that the relative PPV ratio equals 1 if its true value is at least 1.8–2.0, depending on the couple of factors considered.

To calculate the sample size necessary for biomarkers pivotal evaluation (expressed on a continuous scale), minimally acceptable and desirable levels of typical performance measures of interests, such as the true-positive rate (TPR) and the false positive rate (FPR) have been defined. For general population screening, the FPR must be quite low to avoid huge numbers of people undergoing unnecessary costly medical procedures. Thus a maximally acceptable false-positive rate (FPR0) of 4% (the minimally acceptable specificity is therefore 96%) and a minimally acceptable sensitivity of 80% (TPR0) were hypothesized. The null hypothesis to be rejected is the following: H0: TPR0 ≤ 0.80 or FPR0 ≥ 0.04.

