The sample size required with an 80% power (alpha = 5%) and assuming desirable true-positive rate and false-positive rate of TPR1 = 0.90 and FPR1 = 0.05, respectively, was of 179 cases and 537 controls. Sample size computation was based on theory on the Receiver Operating Characteristic (ROC) curve.

Assuming an annual BC detection rate (DR) of 0.006 in the first year and 0.005 in the second year of the study (therefore the biennial DR considered was 0.011) a total of 233 case patients in the first two years of the study are expected to be observed, thus exceeding the 179 required. These estimates are based on DRs observed in the previous years in the same centers considered in this study (Turin, Biella) [4]. Thus, the molecular analyses will be performed on 233 cases and 699 matched controls. For each case, three control subjects will be selected from the cohort of women, on the basis of the following criteria: no history of cancer, similar age at enrolment (within 5 years), similar race, availability of blood sample, similar date of blood draw.

Moreover, circulating miR-18a, miR-181a, and miR-222 levels - derived from the sister study cohort [21] - on plasma collected from all the women enrolled that have at least one first degree relative with BC will be assessed. The estimated number of this subgroup is 1800 women, 40 of which are expected to develop BC within 18 months, and will therefore belong to the case group.

To assess the predictive ability of the considered criteria (i.e., breast density, absolute risk of developing BC and, lifestyles) in identifying groups of women with different risk levels, the positive and negative predictive values and ratios of predictive values (PPV and PPV ratios) will be calculated for each criterion.

The discrimination ability of single biomarkers will be evaluated by means of the ROC curves, whereas to test if biomarker levels are significantly higher or lower in cases and controls, logistic regression models will be used. To evaluate the association between women’s characteristics or tumor features and biomarker level, linear regression models will be adopted.

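### The discordant counts and 80% power stated for the PPV ratio do not apply to factor pairs that include miRNA, because few recalled women without cancer will have a miRNA value

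*Protocol article*

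**What the plan says.** All references are to the Protocol article.

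Statistical power and analysis introduces the PPV ratio for any pair of factors with the premise "As they are determined on the same subjects, among women with abnormal mammography". The ratio is a cross-product of discordant cancers and discordant non-cancers. The power inputs are "Assuming that 40% of 21,000 enrolled women have a dense breast", 20% with a given level of the absolute-risk score, "50% a lifestyle risk and 20% a given miRNA", and "that 11‰ of study women carry BC and that the overall PPV of mammography is 20" per cent. From these the section expects 100–120 discordant cancers and 640–740 discordant women with abnormal mammography but no cancer. It states about 80% power (alpha 0.05) if the true ratio is at least 1.8–2.0, depending on the pair.

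The assay plan is narrower. Biomarkers analysis says the molecular work will be "performed blindly on an appropriate case-control sample extracted from the cohort of enrolled women". Statistical power and analysis says "the molecular analyses will be performed on 233 cases and 699 matched controls". Controls come from the cohort and are chosen on cancer history, age, race, availability of blood and date of blood draw; mammography result is not a criterion. The section adds that miR-18a, miR-181a and miR-222 will be measured in all enrolled women with an affected first-degree relative: an estimated 1,800, of whom 40 are expected to become cases.

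The later paragraph on predictive values names only breast density, absolute risk and lifestyles as criteria. Biomarkers are given ROC curves and logistic regression.

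**The concern.** The ratio needs both factors to be known in the same recalled women, with and without cancer. Density, the absolute-risk score and basic lifestyle items are collected in the cohort at enrolment, so the premise is reasonable for them. For miRNA it fails on the non-cancer side: a recalled woman without cancer has a value only if she happens to be drawn as a control or has an affected first-degree relative.

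The power statement nevertheless treats miRNA like the other factors. Comparing criteria by PPV is how the first main aim is assessed (Study aims). A reader who relies on the stated 80% could take a non-significant comparison involving miRNA as evidence of no difference, when the comparison had little chance of detecting one.

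**Working it through.** **Inputs from Statistical power and analysis.** 21,000 women; 11 per 1,000 with cancer; PPV of mammography 20%; prevalences 0.40 (density), 0.20 (absolute-risk score), 0.50 (lifestyle), 0.20 (miRNA); 699 controls; 1,800 family-history women including 40 cases. **Assumptions added here.** Factors independent of each other; two-sided 5% test (sidedness is not stated); controls and family-history women recalled at the cohort rate; a miRNA value for every cancer.

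**1. The plan's own counts**
- Cancers: 21,000 × 0.011 = 231.
- Recalled: 231 / 0.20 = 1,155, of whom 1,155 − 231 = 924 have no cancer.
- Discordant share: p1(1 − p2) + p2(1 − p1). With miRNA this is 0.44 (density), 0.32 (absolute-risk score) and 0.50 (lifestyle).
- Discordant cancers: 231 × share = 102, 74 and 116. The first and third fit the stated 100–120; the second does not.
- Discordant non-cancers if all 924 were assayed: 407, 296 and 462. The stated 640–740 is not reproduced.
- Pairs without miRNA have shares of 0.44 or 0.50, hence 407–462. The mismatch is therefore not specific to miRNA. Reaching 640–740 would take about 640/0.44 = 1,455 to 740/0.50 = 1,480 recalled non-cancers, a PPV of about 13.5–13.7%.
- If the stated counts are accepted, the power step roughly agrees with the text: 80% power is reached at ratios of about 1.77–1.94 for the miRNA pairs, with miRNA as the better factor.

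**2. Recalled non-cancers with a miRNA value**
- Recall rate in women without cancer: 924 / 20,769 = 4.45%.
- Controls: 699 × 0.0445 = 31.1.
- Family-history women who are not cases: 1,760 × 0.0445 = 78.3.
- Together: 109.4. This is an upper figure, since it ignores overlap and refused blood draws, and it applies only to the three miRNAs measured in that group.

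**3. Power.** Wald test on the log ratio, variance 1/c10 + 1/c01 + 1/n10 + 1/n01, where c and n are the discordant cancers and non-cancers in each direction. Ranges run from a ratio of 1.8 to 2.0 and cover either factor being the better one.

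| Pair with miRNA | Discordant non-cancers, controls only | Power | Discordant non-cancers, with family-history group | Power |
|---|---|---|---|---|
| Density | 13.7 | 14.2–19.1% | 48.1 | 29.1–44.5% |
| Absolute-risk score | 10.0 | 13.7–17.3% | 35.0 | 29.2–38.1% |
| Lifestyle | 15.5 | 13.3–18.0% | 54.7 | 26.5–42.5% |

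Worked example (density and miRNA, ratio 2.0, miRNA better, controls only): the miRNA-only share of discordant non-cancers is 0.12/0.44 = 0.273, and of discordant cancers 0.429. The variance is 0.409, so z = 0.693/√0.409 = 1.08 and power = Φ(1.08 − 1.96) = 19%.

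With miRNA as the better factor, the ratio detectable with 80% power is about 6.1–7.8 (controls only) or 2.9–3.4 (with the family-history group).

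**4. Sensitivity.** With about 1,470 recalled non-cancers instead of 924, roughly what 640–740 implies, discordant counts for miRNA pairs are 16–25 or 56–87. Power is still at most about 57%.

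**The case against.** The best defence is that the paragraph on predictive values already omits miRNA, and that the biomarker aim has its own sample-size calculation (179 cases and 537 controls required, 233 and 699 planned), which does not use the PPV-ratio statement. Both points are true. They limit the consequence to one factor in one power statement; neither the cohort size nor the case-control numbers depend on it. They do not remove the conflict, because the power statement still counts miRNA.

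Four stronger readings are tempting, and the document does not support them.
- That miRNA is measured only in cases and their matched controls. The family-history group is assayed too, for three miRNAs. It raises the counts but does not restore the power.
- That pairs with miRNA cannot be analysed. The estimator is a cross-product, so a control sampling fraction unrelated to the factors multiplies both non-cancer cells and cancels. The cells are small, not empty. Selection on family history, which is collected in the short questionnaire that feeds the absolute-risk score, and matching on age do need handling.
- That miRNA will show a PPV near 25% by design, since 233/(233 + 699) = 25%. That would follow from an unweighted PPV in the 1:3 sample, but no such analysis is planned.
- That pairs with SNPs are equally affected. SNPs appear in the general modelling sentence ("polygenic risk score from miRNAs and SNPs will be modeled"), but no SNP prevalence or pair enters the power statement.

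It is also fair to say that not all of the gap between 640–740 and 10–55 comes from the assay plan. Even with all 924 recalled non-cancers assayed, the miRNA pairs would give 296–462.

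**Conclusion.** The power statement is wrong as written for pairs that include miRNA. Discordant recalled non-cancers with a miRNA value number about 10–16 from controls, or at most 35–55 with the family-history group, against 640–740 stated. Power at a ratio of 1.8–2.0 is about 13–19% or 27–45%, against about 80% stated. The ratio remains estimable in assayed women, with low precision.

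The figures rest on independent factors, a two-sided 5% test and recall of assayed women at the cohort rate. Incomplete blood donation, which the Discussion names as a critical aspect, would tend to lower the family-history count. The conclusion does not depend on the exact recall rate: power stays below 80% when the recalled non-cancers are raised to the level that 640–740 implies.

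**What to change.** 1. Remove miRNA from the PPV-ratio power statement, or give separate discordant counts and power for pairs with miRNA in the women actually assayed. Align the statement with the later list of criteria (density, absolute risk, lifestyles).
2. If predictive values or PPV ratios for miRNA are to be reported, weight by the inverse of the sampling probability. Base the probabilities on women with a stored blood sample rather than the full cohort, account for the matching, and give family-history women their own probability, since all who gave plasma are assayed for the three miRNAs.
3. Separately, recheck 640–740. The stated inputs give 924 recalled non-cancers in total and 407–462 discordant for pairs without miRNA. Correct either the counts or the inputs, and restate the power for all pairs.

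The cost is wording, a short recalculation and, if miRNA predictive values are reported, a standard weighted analysis. The stated power for miRNA pairs becomes less favourable. No new assays or participants are needed.

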## Discussion

This study has been designed to achieve several outcomes: to collect necessary information to compare performance of BC evaluation criteria; to acquire necessary data to design stratified BC screening programs; to evaluate feasibility and impact of different screening strategies; to establish a conspicuous bio-bank useful to accurately validate selected biomarkers (and future novel ones) .

Although follow up is planned for 10 years, preliminary results will be available at the end of the three years of study duration. The above mentioned results could contribute in defining BC screening protocols on different risk factors other than age only, as it currently is.

Securely a critical aspect of the study could be represented by the acceptance of women to undergo a blood test. This point, though difficult, is a key point of the project as it will allow us to establish the bio-bank. To try and overcome these barriers and encourage women participation we are intensely working on communication and organization.

As concerns communication, very detailed information materials strongly emphasizing the goal of blood samples collection and its impact on the final outcomes of the study have been arranged. This material clearly explains the relevance of the personal history of each woman in terms of potential BC risk factors, so encouraging participants in following the whole study path.

The information material is designed to encourage, in a friendly and direct way, women to provide information about their lifestyle and a blood sample, so contributing to improve BC prevention strategies: a precious gift not only to themselves but also to other women.

Furthermore, a call centre has been be set up allowing women to get further information and to speak directly with a dedicated health operator. Particular attention is given to the training of health personnel interacting with women at the time of the screening, making them able to provide adequate and correct information. In particular, since the screening invitation letter is signed by GPs, they receive special educational interventions.

Regarding logistic aspects, we are giving participants the opportunity either to undergo blood drawing immediately after mammography or to fix a suitable appointment, facilitated by the fact that fasting is not necessary.

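### The aim 1 power counts 231 cancers by adding two yearly detection rates; one screen per woman gives 105–126, and about 80% two-sided power at a ratio of 1.8–2.0 is then not reached

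*Protocol article*

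**What the plan says.** All of this is in the Protocol article. Under Statistical power and analysis, aim 1 compares risk criteria in pairs among women with an abnormal mammogram, using a cross-product of discordant cancers and discordant non-cancers.

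- The inputs begin: "Assuming that 40% of 21,000 enrolled women have a dense breast, 20% a certain Petracci score, 50% a lifestyle risk and 20% a given miRNA". To these are added a cancer yield of 11 per 1,000 and a mammography PPV of 20%: "that 11‰ of study women carry BC and that the overall PPV of mammography is 20%, some 100–120 discordant cancers".
- The result is "some 100–120 discordant cancers and 640–740 discordant women with abnormal mammography but no cancer are expected for the considered couples of factors", with about 80% power at alpha 0.05 when the true ratio is at least 1.8–2.0. Whether alpha is one- or two-sided is not stated.
- Later in the same section, the case count for aim 2 shows where the yield comes from: "Assuming an annual BC detection rate (DR) of 0.006 in the first year and 0.005 in the second year of the study". The two are summed to 0.011, called the biennial rate, and used to expect 233 cases in the first two years.

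Background says that most Italian programmes invite women aged 50–69 every two years. Study setting gives enrolment from July 2015 to December 2017, a planned duration of three years, and ten further years of follow-up through the screening archives. Discussion says that "preliminary results will be available at the end of the three years of study duration".

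**The concern.** The estimator works on women recalled from a mammogram and is paired with the PPV of mammography. The yield that matches it is cancers found per screen. Eleven per 1,000 of 21,000 women counts every woman in both yearly rates. A woman screened every two years contributes to both only after a second mammogram, and many women enrol too late to have one within the study.

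The smaller count, the discordant cancers, limits the power of this cross-product. If that count is roughly halved, the only power statement for the first main aim no longer describes what the study can detect, at least for results at three years.

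**Working it through.** **Inputs from the article:** 21,000 women; prevalences 0.40 (density), 0.20 (score), 0.50 (lifestyle); 11 per 1,000; PPV 20%; yearly rates 0.006 and 0.005; stated discordant non-cancers 640–740.

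**Assumptions made here:** factors are independent; two-sided 5% Wald test of the log ratio; the yearly rates of 0.005–0.006 serve as rates per screen.

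**1. Reproducing the stated counts.** Cancers: 21,000 × 0.011 = 231. The discordant share is p1(1−p2) + p2(1−p1):
- density/score: 0.40×0.80 + 0.20×0.60 = 0.44
- density/lifestyle: 0.40×0.50 + 0.50×0.60 = 0.50
- lifestyle/score: 0.50×0.80 + 0.20×0.50 = 0.50

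Discordant cancers are 231 × 0.44–0.50 = 102–116, which matches the stated 100–120. The miRNA, at 20%, gives the same shares as the score when paired with density or lifestyle. Score with miRNA has a share of 0.32, or 74 cancers, and lies outside the stated range even at 11 per 1,000.

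The stated non-cancers do not follow from PPV 20%, which gives 231 × 4 = 924, and 924 × 0.44–0.50 = 407–462. The stated 640–740 needs about 1,470 non-cancers, a PPV of 231/1,701 = 14%. Both versions are carried below.

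**2. Reproducing the stated power.** SE² of the log ratio is the sum of 1/cell over the four discordant cells. Power is Φ(ln R/SE − 1.96). For density over lifestyle at R = 2.0, non-cancers split 0.40/0.60 (294 and 441). The odds among cancers are 2 × 0.40/0.60 = 1.333, so 115.5 cancers split into 66.0 and 49.5. Then SE² = 1/66 + 1/49.5 + 1/294 + 1/441 = 0.0410, SE = 0.2025, and power = Φ(3.42 − 1.96) = 0.93. The claim reproduces in the better directions (table, second column).

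**3. One screen per woman.** 21,000 × 0.005–0.006 = 105–126 cancers. Discordant: 105 × 0.44 = 46 up to 126 × 0.50 = 63. Same example with 63 cancers (36 and 27): SE² = 1/36 + 1/27 + 1/294 + 1/441 = 0.0705, SE = 0.2655, power = Φ(2.61 − 1.96) = 0.74.

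In the table, 231 cancers are paired with 1,470 non-cancers. The ranges for one screen run from 105 cancers with non-cancers from PPV 20% (420) to 126 cancers with 1,470 non-cancers.

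| Direction | 231 cancers: power at 1.8 / 2.0 | One screen: power at 1.8 | One screen: power at 2.0 | One screen: ratio for 80% |
|---|---|---|---|---|
| Density over lifestyle | 0.83 / 0.93 | 0.47–0.61 | 0.60–0.74 | 2.1–2.4 |
| Score over density | 0.76 / 0.89 | 0.40–0.53 | 0.53–0.68 | 2.2–2.6 |
| Score over lifestyle | 0.76 / 0.89 | 0.40–0.53 | 0.53–0.69 | 2.2–2.5 |
| Lifestyle over density | 0.75 / 0.86 | 0.41–0.52 | 0.51–0.64 | 2.4–2.9 |
| Density over score | 0.56 / 0.68 | 0.28–0.36 | 0.36–0.45 | above 3.8 |
| Lifestyle over score | 0.50 / 0.61 | 0.25–0.32 | 0.31–0.39 | above 6 |

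The upper ends are generous: 126 cancers with 1,470 non-cancers is a PPV of 126/1,596 = 8%, not 20%.

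**4. A partial second round (assumption).** Suppose women enrolled in the first 12 of 30 months (40%) are screened again within the three years. Cancers are then 21,000 × 0.005 × 1.4 = 147 up to 21,000 × (0.006 + 0.4 × 0.005) = 168, with 65–84 discordant. Density over lifestyle has power of about 0.75–0.85 at 2.0 and at most 0.72 at 1.8. The next best directions, score over lifestyle and score over density, peak at 0.79 at 2.0.

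**The case against.** The strongest reply is that nothing limits aim 1 to the enrolment mammogram. The article calls 0.011 a biennial rate and counts cases over two years. It follows the cohort for ten more years and promises only preliminary results at three. It never calls 0.005–0.006 a rate per screen. The two-year interval is given for most programmes at ages 50–69, while this cohort is 46–67. On that view the arithmetic is right and only the number of rounds is unstated.

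This stands in part. A reader might infer that the plan analyses one screen and is wrong as computed. The documents do not say so, although the short questionnaire and breast density are collected at the enrolment visit. What does not survive is the two-year timing: with 30 months of enrolment and mostly two-yearly screening, the full cohort cannot yield both rates in the first two years.

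Four other strong readings should be resisted:

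- **No couple can reach 80%.** This needs a two-sided alpha and no second-round cancers. A null of equality suggests two-sided, but the article does not say. One-sided, with the stated non-cancers, density over lifestyle reaches about 0.81–0.83 at 2.0 for 115.5–126 cancers.
- **The lowest powers are caused by the yield.** Density over score and lifestyle over score already miss 80% at 231 cancers.
- **A non-significant ratio will be taken as equivalence.** The article says nothing of the kind.
- **A two-round analysis has a fixed calendar date.** That would need a screening interval for the whole cohort, which is not given.

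**Conclusion.** The concern holds in conditional form. The stated 100–120 discordant cancers, and the power built on them, need two yearly detection rates from every one of 21,000 women. The enrolment period and usual screening interval do not allow that within the first two years. With one screen per woman, discordant cancers are about 46–63, and two-sided power misses 80% at 1.8–2.0 for every couple examined. With a partial second round, only density over lifestyle reaches about 80%, and only at 2.0.

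These sizes rest on independence of the factors, a two-sided Wald test and the yearly rates standing in for rates per screen. The choice of non-cancer count changes the figures but not the conclusion.

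**What to change.** In Statistical power and analysis, state which screening rounds supply the cancers for aim 1 and whether alpha is one- or two-sided.

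- **If only the enrolment screen counts:** replace 11 per 1,000 with 5–6 per 1,000. Restate discordant cancers as about 46–63 and give the detectable ratio for each couple and direction.
- **If two rounds are meant:** say so, and time the aim 1 analysis to when the cohort has completed the second round. Label the three-year results as preliminary and lower powered.

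While the paragraph is open, reconcile the 640–740 discordant non-cancers with the 20% PPV.

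The cost is text and a recalculation. Under the first option the stated detectable ratio becomes less favourable; under the second the full-power analysis comes later. Enrolment and data collection are unaffected.

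### The 640–740 discordant non-cancers contradict the stated 20% PPV (407–462 follow from the inputs), and the 80% power at a ratio of 1.8–2.0 holds only for some couples and directions

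*Protocol article*

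**What the plan says.** The Protocol article, Statistical power and analysis, compares pairs of risk factors by a ratio built from discordant women only, that is, women positive for one factor and negative for the other. The comparison is made within recalled women: "As they are determined on the same subjects, among women with abnormal mammography".

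The factor prevalences are given as "40% of 21,000 enrolled women have a dense breast, 20% a certain Petracci score, 50% a lifestyle risk and 20% a given miRNA". Two more inputs complete the set: a cancer prevalence of 11‰ in the cohort, and a mammography PPV of 20%. The result drawn from these inputs reads: "some 100–120 discordant cancers and 640–740 discordant women with abnormal mammography but no cancer are expected for the considered couples of factors".

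On power, the article claims: "the study has about 80% power to reject (alpha = 0.05) the null hypothesis that the relative PPV ratio equals 1". The smallest true ratio to which this claim applies is put at 1.8 to 2.0, varying by couple.

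It does not list the couples considered, and it does not state the sidedness of the test, the correlation between factors, or which factor of a couple is taken to have the higher PPV.

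**The concern.** The inputs and the result stand in the same sentence, so the counts can be checked directly. With a PPV of 20%, recalled women without cancer outnumber recalled cancers by 4 to 1. If the factors split both groups alike, the discordant women must show the same 4 to 1. The stated ranges stand at 640/100 = 6.4 and 740/120 = 6.2 to 1.

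The estimator is the odds ratio of a 2 × 2 table of discordant women. Its precision depends on the smallest cell, and so on which factor is better. One range of 1.8–2.0 indexed only by couple hides this.

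This is the only power statement for the first main aim (Study aims), which compares the criteria by PPV. A reader cannot tell whether the PPV or the count is wrong. A null result for density or lifestyle against a rarer factor could also be read as adequately powered when it was not.

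**Working it through.** **Inputs (all from Statistical power and analysis).** N = 21,000; cancer 11‰; PPV 20%; prevalences: density 40%, Petracci score 20%, lifestyle 50%, miRNA 20%; alpha 0.05.

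**Assumptions.** Factors are independent; the stated prevalences apply to recalled women; all 231 cancers are among the recalled.

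**Step 1: base counts.** Cancers = 21,000 × 0.011 = 231. Recalled = 231/0.20 = 1,155. Non-cancers = 1,155 − 231 = 924.

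**Step 2: discordant counts.** Discordant share d = p(1 − q) + q(1 − p).

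| Couple | d | Cancers (231 × d) | Non-cancers (924 × d) |
|---|---|---|---|
| Density with Petracci or miRNA | 0.44 | 102 | 407 |
| Lifestyle with density | 0.50 | 116 | 462 |
| Lifestyle with Petracci or miRNA | 0.50 | 116 | 462 |
| Petracci with miRNA | 0.32 | 74 | 296 |

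The stated 100–120 cancers are reproduced for five of the six couples, so this appears to be the method used. The stated 640–740 non-cancers are reproduced for none.

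**Step 3: what 640–740 would need.** 640/0.44 = 1,455 and 740/0.50 = 1,480 non-cancers. The PPV would then be 231/(231 + 1,455) = 13.7% or 231/(231 + 1,480) = 13.5%.

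**Step 4: other readings.**
- *All 1,155 recalled women as base:* 0.32, 0.44 and 0.50 of 1,155 give 370, 508 and 578.
- *Whole cohort as base:* more than 6,600.
- *Dependent factors:* the largest possible discordant share is min(p + q, 2 − p − q). Applied to 924 it gives 554 for density with a 20% factor, 370 for the two 20% factors, 647 for lifestyle with a 20% factor and 832 for lifestyle with density. So 640 is out of reach for three couples. Where it can be reached, 640/924 = 0.69 of the women are discordant. The same share of 231 cancers is 160, outside 100–120.

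**Step 5: power with the recomputed counts, two-sided 5%.** Let s be the share of discordant non-cancers that are positive for the commoner factor: s = p(1 − q)/d. Among discordant cancers the odds s/(1 − s) are multiplied by R if the commoner factor is better and divided by R if the rarer one is. Wald power = Φ(ln R/SE − 1.96), with SE² the sum of the reciprocals of the four discordant cells.

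Example, density against a 20% factor, R = 2.0: s = 0.32/0.44 = 0.727, odds 2.667.
- *Density better:* odds 5.333, share 0.842. Cells are 85.6 and 16.0 (cancers), 295.7 and 110.9 (non-cancers). SE = 0.294; ln 2/0.294 − 1.96 = 0.40; power 66%.
- *Rarer factor better:* odds 1.333, share 0.571. Cancer cells are 58.1 and 43.6. SE = 0.229; ln 2/0.229 − 1.96 = 1.06; power 86%.

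All couples, pooled two-proportion test / Wald:

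| Couple and better factor | Power at 1.8 | Power at 2.0 | Ratio detectable at 80% |
|---|---|---|---|
| Density better than a 20% factor | 55% / 54% | 69% / 66% | 2.22 / 2.38 |
| 20% factor better than density | 72% / 72% | 85% / 86% | 1.91 / 1.90 |
| Lifestyle better than density | 75% / 72% | 87% / 84% | 1.88 / 1.92 |
| Density better than lifestyle | 81% / 80% | 92% / 91% | 1.79 / 1.80 |
| Lifestyle better than a 20% factor | 49% / 48% | 62% / 59% | 2.41 / 2.69 |
| 20% factor better than lifestyle | 71% / 72% | 84% / 86% | 1.93 / 1.91 |
| Petracci against miRNA | 60% / 59% | 74% / 72% | 2.11 / 2.17 |

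**Step 6: effect of the count error alone.** With 640–740 non-cancers the pooled detectable ratios are 2.14–2.15 (density better than a 20% factor), 2.32–2.34 (lifestyle better than a 20% factor), 1.85–1.86 and 1.88–1.89 (the reverse directions), and 2.01–2.02 for the two 20% factors where 2.11 was found. Each differs from Step 5 by 0.1 or less.

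**The case against.** No reading rescues 640–740 for all couples at a PPV of 20%. The strongest objections concern power, and several stand.

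- *The claim is reproduced in one direction.* With the rarer factor better, and for density with lifestyle either way, the detectable ratios are 1.79–1.93 even with the smaller counts. A reader might infer that the 80% claim is simply false, or that the first aim is underpowered as a whole. The article does not support that: it states no direction, and one natural direction gives its range.
- *Sidedness is not stated.* One-sided (pooled), density over a 20% factor reaches 2.00, the two 20% factors 1.93, and only lifestyle over a 20% factor misses, at 2.12. Two-sided is the usual default, but it is an assumption here.
- *The larger ratios depend on the method.* If the number of discordant cancers is allowed to grow under the alternative, 2.22 and 2.41 become 2.06 and 2.21, and the two 20% factors fall to 1.98. No single set of detectable ratios is the right one.
- *Petracci with miRNA may not be meant.* The stated cancer range fits every other couple, and a later paragraph of the same section names only density, absolute risk and lifestyles for the PPV ratios. Yet the formula is offered for any couple of factors, miRNA included. The scope is unclear; an omission is not shown.
- *The count error hardly affects power.* It is tempting to blame the shortfall on the inflated non-cancers. Step 6 shows otherwise: the number of cancers and the split of the discordant women drive it.

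**Conclusion.** The count contradiction is certain. At a PPV of 20% and independent factors, the discordant non-cancers are 407–462 for the couples that match the stated cancers, not 640–740. If Petracci with miRNA is among the couples, its 74 cancers and 296 non-cancers lie outside both stated ranges. Either the PPV or the count is wrong, and the text does not show which.

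The power claim is incomplete, and not wrong throughout. At two-sided 5% it holds when the rarer factor has the higher PPV and for density against lifestyle. It does not hold when density or lifestyle is better than a 20% factor: the detectable ratio is then about 2.2–2.4 (pooled) or 2.4–2.7 (Wald), with power at 2.0 of about 59–69%. For the two 20% factors the detectable ratio is about 2.1–2.2. These power figures rest on independence, fixed numbers of discordant cancers and a two-sided test. A one-sided test or shifting cancer counts brings them closer to 2.0, but neither alone brings lifestyle over a 20% factor within the range.

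**What to change.** 1. Correct the discordant non-cancers to about 410–460, adding 74 cancers and 296 non-cancers for Petracci with miRNA if that couple is included. If a PPV of about 13.6% was used in the calculation, correct the PPV instead and keep 640–740 for the other couples.
2. List the couples considered, and state the test, its sidedness and the independence assumption.
3. Limit the claim of about 80% power at 1.8–2.0 to the couples and direction for which it holds, and give the larger detectable ratio for the other direction, computed with the stated test.

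The cost is a few restated figures. Enrolment, design and analysis do not change; the stated power becomes somewhat less favourable.
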